#### Data analysis plan

Analyses will test whether participants who played the game (treatment arm) relative to control participants who have not received any encouragement to play the game:Improved knowledge about SRH care, including menstruation, menstrual hygiene, fertility awareness, and SRH/menstrual management products.Improved attitudes, confidence, and decision support for managing her self-care, SRH, negotiating consent and contraceptive use, and accessing/using DTC information, products, and care.Improved assertion of self-identity through DTC linkages to career, safety, and personal well-being resources, and improved self-efficacy.

Analysis of the quantitative study data will be conducted using STATA and SPSS where appropriate. Descriptive analysis will be performed for all variables, and unadjusted comparisons between experimental and control arms will be conducted. Descriptive statistics will be performed, including frequencies, means, and standard deviations. In addition, chi-square tests and t-tests will be used to examine associations in the data. A probability value of less than 0.05 will be considered statistically significant for all statistical tests conducted. Continuous variables will be tested for normality, and non-normal values will be categorised or transformed appropriately.

The following two analyses will be done to satisfy the objective of the study:Univariate descriptive analysis such as frequency, percentages, the mean, and standard deviation will be computed for different background characteristics and knowledge, attitude, and practice (KAP) variables.KAP variables will be analyzed using Z-test/t-test for encouragement and control arms in two points from the same respondent.The net change in KAP and its significance will be calculated using difference-in-difference (DID) analysis. The DID analysis will be done using the following formula. (See Table 5)

**Table 5 Tab5:** Difference-in-difference analysis pathway in RCT

	Experimental arm (s = 2)	Control arm (s = 1)	Difference (s)
Baseline (t = 1)	Y_12_	Y_11_	Y_21_ –Y_11_
Follow-up (t = 2)	Y_22_	Y_21_	Y_22_ –Y_12_
Difference (t)	Y_22_ –Y_21_	Y_12_ –Y_11_	Net change (DID) = (Y_22_ – Y_21_) – Y_12_ – Y_11_

The level of significance of DID will be tested using the below equation through regression analysis.$${\text{Y }} = {\text{ a }} + {\text{ b}}_{{{\text{1s}}}} + {\text{ b}}_{{{\text{2t}}}} + {\text{ b}}_{{{\text{3s}}*}}$$

where.

Y = dependent/response variable.

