a = constant.

s and t are study arm and time, respectively.

b_1_ and b_2_ are slopes for the study arm and time, respectively.

b_3_ = treatment effect.

s*t is a dummy variable indicating treatment status.

The significance level of the test will be measured using a p-value < 0.05 (95% level of significance as per the sample size estimation).

The primary comparison of the binary outcomes between intervention groups at baseline and follow-up will use mixed-effects longitudinal logistic regression, with random effects for the individual over time. The baseline will be included as a time point only. A categorical time effect will be used (profile model). A “difference-in-differences” analysis will compare the treatment arms. Statistically, this amounts to testing for an interaction between time and treatment arm in the longitudinal model. Since the treatment assignment is at random, this “unadjusted” analysis will provide a causal effect of the intervention. However, we will also conduct secondary analyses, adjusting for potentially relevant covariates (e.g., age, education, etc.), in addition to time and treatment arm, using backward model selection at the α = 0.15 threshold level. These secondary analyses may improve the precision (power) of estimating the treatment effect and reduce any bias due to random imbalances between arms.

The primary analyses will use an intent-to-treat approach and analyze all subjects according to a randomized group. For subjects missing the follow-up survey, we will impute data from the lower (worse) half of the distribution by the arm (conservative approach). We will also conduct dose analyses, in which we include only those subjects who complete the full intervention. Analyses will use data only for outcomes; (a) increased comprehensive contraceptive knowledge, (b) MHM (c) negotiation and self-efficacy. We will conduct exploratory analyses using outcomes.

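### Table 5 prints the net-change formula without its second bracket, so the result is the difference-in-differences minus twice the control baseline; two cell labels are also exchanged relative to the margins

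*Protocol article*

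**What the plan says.** All of this is in the Data analysis plan of the protocol article.

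- The net change in the knowledge, attitude and practice variables is to be obtained by DID, and the text points to Table 5 for the calculation: "The DID analysis will be done using the following formula".
- Table 5 sets the arm index in its column heads: "Experimental arm (s = 2") for the experimental arm, and s = 1 for control. The rows carry the time index, 1 for baseline and 2 for follow-up.
- The cells, experimental arm first, read "Baseline (t = 1) Y_12_ Y_11" and "Follow-up (t = 2) Y_22_ Y_21".
- The margin headed Difference (s) holds Y21 − Y11 at baseline and Y22 − Y12 at follow-up. The margin headed Difference (t) holds Y22 − Y21 for the experimental arm and Y12 − Y11 for control.
- The corner cell gives the result: "Net change (DID) = (Y_22_ – Y_21_) – Y_12_ – Y_11".
- The test of the DID is a separate step: "The level of significance of DID will be tested using the below equation through regression analysis". In that regression b3, the coefficient of the arm-by-time product, is the treatment effect.
- The primary comparison of the binary outcomes is a mixed-effects longitudinal logistic regression. For the DID, "this amounts to testing for an interaction between time and treatment arm in the longitudinal model".

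**The concern.** There are two separate faults in one table.

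First, a DID subtracts one difference from another, so the last term must come back with a plus sign. The corner cell brackets the first pair and leaves the second open, which makes it a minus sign.

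Second, the cell labels put time first and arm second, while the margins make sense only with arm first and time second. A reader who takes the margins literally from the printed cells would report changes over time as differences between arms, and the reverse.

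The formula is not background text: the plan says the DID will be calculated with it. The selected outcome indicators are percentages of girls, many of them likely to be well above zero at baseline, so a net change tabulated literally from Table 5 would be visibly wrong. It would also disagree with the regression coefficient meant to test the same quantity.

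**Working it through.** **Inputs.** The four cells as labelled in Table 5: experimental baseline Y12, experimental follow-up Y22, control baseline Y11, control follow-up Y21. The protocol gives no baseline rates or effect sizes, so every percentage below is an assumption.

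**Step 1: the correct quantity from the printed cells.**

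DID = (experimental change) − (control change) = (Y22 − Y12) − (Y21 − Y11) = Y22 − Y12 − Y21 + Y11.

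**Step 2: the printed formula.**

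Printed = (Y22 − Y21) − Y12 − Y11 = Y22 − Y21 − Y12 − Y11.

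**Step 3: the gap.**

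Printed − DID = −Y11 − Y11 = −2 × Y11.

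A numerical check on 200,000 random sets of cells agreed with this identity to rounding error (largest deviation about 4 × 10⁻¹⁶).

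**Step 4: size and sign.** A percentage cannot be negative, so the printed value is never above the true one, and it is too low whenever Y11 > 0. The sign reverses only when 0 < DID < 2 × Y11. A negative DID stays negative but is exaggerated.

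| Assumed true DID (points) | Assumed control baseline Y11 | Printed formula = DID − 2 × Y11 (points) |
|---|---|---|
| +10 | 2% | 10 − 4 = +6 |
| +10 | 5% | 10 − 10 = 0 |
| +10 | 10% | 10 − 20 = −10 |
| +10 | 40% | 10 − 80 = −70 |
| +10 | 60% | 10 − 120 = −110 |
| +5 | 2% | 5 − 4 = +1 |
| +5 | 40% | 5 − 80 = −75 |
| −5 | 10% | −5 − 20 = −25 |

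**Step 5: the margins against the cells.** Assume 40% at baseline in both arms, and at follow-up 60% in the experimental arm and 45% in control. Then Y12 = 40, Y11 = 40, Y22 = 60 and Y21 = 45.

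| Margin | Correct from the cells | As printed |
|---|---|---|
| Between arms, baseline | Y12 − Y11 = 0 | Y21 − Y11 = 5 |
| Between arms, follow-up | Y22 − Y21 = 15 | Y22 − Y12 = 20 |
| Over time, experimental | Y22 − Y12 = 20 | Y22 − Y21 = 15 |
| Over time, control | Y21 − Y11 = 5 | Y12 − Y11 = 0 |

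The printed margins would show a 5-point baseline imbalance where there is none, and no change in a control arm that rose by 5 points.

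**Step 6: the two faults are independent.** Exchanging Y12 and Y21 leaves Y22 − Y21 − Y12 + Y11 unchanged, so the labelling slip drops out of the net change. It also leaves the printed formula unchanged, so relabelling does not repair the missing bracket. In the example the true DID is 20 − 5 = +15 points and the printed formula gives 60 − 45 − 40 − 40 = −65. With the bracket restored, (60 − 45) − (40 − 40) = +15 under either labelling.

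**Step 7: the regression.** With s and t coded 1 and 2 as in Table 5, the coefficient of s × t in the saturated linear model is Y22 − Y12 − Y21 + Y11, the correct DID. For the example it is again +15 points. The bracket error does not reach it.

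**The case against.** The strongest reply is that no test and no primary estimate runs through the hand formula. The significance of the DID comes from a regression whose arm-by-time coefficient is correct, and the primary comparison is an interaction in a longitudinal logistic model. The intended formula is also plain from the table: the bottom row prints the two differences in adjacent cells, and the corner cell is meant to be one minus the other. An analyst who saw −70 points when the experimental arm had improved more would stop and look. On the labels, rows and columns are named in words, and the four mismatched margins trace back to a single exchange of two subscripts.

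Most of this stands, and it limits the point. It does not remove it: the plan names Table 5 as the way to calculate the net change, and the expression is wrong as written. The logistic interaction is on the log-odds scale, so Table 5 is also where a reader would look for the definition of a net change in percentage points.

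Three stronger readings are tempting and should be set aside.

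- A reader might infer that the trial's treatment effect or its p-value is corrupted. Both model-based analyses are free of the error, so the documents do not support that.
- A reader might infer that the sign always reverses. It does so only when 0 < DID < 2 × Y11.
- A reader might infer that the margin conflict contributes to the wrong net change. It cancels.

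The plan calls s × t a dummy variable, although with 1/2 coding the product takes the values 1, 2 or 4. The word is loose, but the linear coefficient is the same, so nothing in the estimate depends on it.

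Loss of the bracket in text extraction is possible, and the equation below the table is visibly damaged. It is unlikely here, because the first pair in the same cell kept its brackets. The typeset table should still be checked.

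**Conclusion.** The point holds as a definite but contained error. The net change as printed equals the true DID minus 2 × Y11. That result is algebra and needs no assumption beyond the printed symbols. The sizes shown (for a true DID of +10 points: +6, −10 and −70 at control baselines of 2%, 10% and 40%) rest on assumed rates and serve only to show the range. The exchange of Y12 and Y21 relative to the margins is a second, separate slip that mislabels the intermediate differences only. What is at risk is any net change or margin tabulated literally from Table 5. This is a minor correction, to be made before such a table is produced or the formula is reused.

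**What to change.** 1. In the corner cell of Table 5, print Net change (DID) = (Y22 − Y21) − (Y12 − Y11).
2. Index the cells by arm first and time second: experimental baseline Y21, experimental follow-up Y22, control baseline Y11, control follow-up Y12. This exchanges the two off-diagonal labels, and all four printed margins then hold without further change.
3. Optionally, code arm and time as 0/1 so that describing s × t as a dummy variable is accurate. This does not change the linear interaction coefficient.

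The cost is the correction of one table. Design, sample size, data collection and the model-based analyses are not affected.

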### RCT study

#### Sample size

The study proposes recruiting 1,950 participants from three sites: 650 girls each from Patna, Jaipur, and Delhi NCR for in-person interviews. In addition, 60 girls (n = 20 each from Patna, Jaipur, and Delhi NCR) will be recruited purposively from the encouragement arm of 975 participants for qualitative in-depth interviews. During the encouragement design activity, half of the participants (i.e., 325 girls each from Patna, Jaipur, and Delhi NCR) will receive nudges/encouragement to play the game.

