### Follow-up survey

Following the ten-week intervention period/encouragement, participants will be assessed through the administration of the follow-up survey. All procedures related to informed consent, confidentially, data privacy, and risk mitigation will be followed, as will been done in the baseline. Resurveying participants in this manner will enable us to create a panel of individual girls, in which each girl is observed over two time points. In the endline survey, we will collect data using the same survey tool, with an additional section on gameplay and game-related elements, including brand recall of in-game links to products and services.

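### The plan gives two significance tests for the same difference-in-difference effect, and the regression without a participant term, run as written, has standard errors that are too large

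*Protocol article*

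**What the plan says.** All of this is in the protocol article.

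- Data analysis plan, on the net change in the knowledge, attitude and practice (KAP) variables: "The level of significance of DID will be tested using the below equation through regression analysis". The equation has a constant, a term for arm, a term for time and their interaction. The interaction is explained as "s*t is a dummy variable indicating treatment status", and its coefficient is named as the treatment effect. The threshold follows: "The significance level of the test will be measured using a p-value < 0.05 (95% level of significance as per the sample size estimation".
- The next paragraph of that section: "The primary comparison of the binary outcomes between intervention groups at baseline and follow-up will use mixed-effects longitudinal logistic regression". This model has a random effect for the individual, and its difference-in-difference (DID) test is again the time-by-arm interaction.
- The same section also says: "KAP variables will be analyzed using Z-test/t-test for encouragement and control arms in two points from the same respondent".
- Follow-up survey: the resurvey is meant to "create a panel of individual girls, in which each girl is observed over two time points".
- Outcomes measures, Table 4: all three groups of indicators are percentages of girls, so the listed outcomes are binary.

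Apart from the label primary on the mixed model, nothing ranks the two tests. The regression is described with no participant term and no clustered standard error.

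**The concern.** Both tests address the same quantity, the arm-by-time interaction, on the same binary indicators. They do not treat the data alike. The mixed model allows for the two answers of one girl being correlated; the regression, as written, does not.

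A DID is a comparison of within-girl changes. When a girl's two answers are positively correlated, her change varies less than the difference of two unrelated answers would. An analysis that ignores this overstates the standard error. An analyst who follows the sentence on testing the DID could therefore report a real effect of the game as non-significant while the mixed model finds it significant. The two results are also on different scales: percentage points for a linear regression, and a conditional odds ratio for the mixed model.

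**Working it through.** **Inputs.** From the Sample size section: "The study proposes recruiting 1,950 participants from three sites: 650 girls each from Patna, Jaipur, and Delhi NCR for in-person interviews", and "half of the participants (i.e., 325 girls each from Patna, Jaipur, and Delhi NCR) will receive nudges/encouragement to play the game". So 3 × 650 = 1,950 girls in total and 3 × 325 = 975 per arm, which agree. Two surveys per girl give 2 × 1,950 = 3,900 rows. Alpha is 0.05, taken as two-sided because the article does not say. The article gives no within-girl correlation, so rho is assumed over 0 to 0.7. The calculation takes a prevalence p that is the same in all four arm-by-time cells, and complete data. The article shows no power figure that could be reproduced first.

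**Standard errors.** With n = 975 per arm, the variance of the mean change in one arm is 2p(1−p)(1−rho)/n. The DID is the difference between two such means.

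- Allowing for pairing: SE = √[4p(1−p)(1−rho)/n].
- Pooled, rows taken as independent: SE = √[4p(1−p)/n].
- Ratio, pooled to paired: 1/√(1−rho), whatever p is.

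At p = 0.5 the pooled SE is √(1/975) = 0.0320, or 3.20 percentage points.

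**True type I error of the pooled test:** 2 × [1 − Φ(1.96/√(1−rho))].

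| rho (assumed) | Paired SE (points) | Pooled/paired | True type I error, pooled | Observed DID significant when paired only (points) |
|---|---|---|---|---|
| 0 | 3.20 | 1.00 | 5.0% | none |
| 0.2 | 2.86 | 1.12 | 2.8% | 5.61 to 6.28 |
| 0.3 | 2.68 | 1.20 | 1.9% | 5.25 to 6.28 |
| 0.5 | 2.26 | 1.41 | 0.6% | 4.44 to 6.28 |
| 0.7 | 1.75 | 1.83 | 0.03% | 3.44 to 6.28 |

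The last column runs from 1.96 × paired SE to 1.96 × pooled SE, at p = 0.5. At p = 0.3 the pooled SE is 2.94 points; the ratios and type I errors do not change.

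**Power.** Take an effect with 80% power under the paired analysis, that is 2.80 paired SEs. The power of the pooled test is Φ(2.80 − 1.96/√(1−rho)).

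- rho 0.3: 1.96/√0.7 = 2.34, and Φ(0.46) = about 68%.
- rho 0.5: 1.96/√0.5 = 2.77, and Φ(0.03) = about 51%.

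**Simulation against the mixed model itself.** 400 replicates per scenario, 975 per arm, random-intercept logistic data, 40% at baseline and 45% in controls at follow-up.

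| Scenario | Pooled regression significant | Paired or girl-clustered | Mixed logistic | Pooled and mixed disagree |
|---|---|---|---|---|
| No effect, rho about 0.47 | 0.7% | 4.5% | 4.8% | 4.0% |
| True DID 6 points, rho about 0.47 | 49.7% | 74.8% | 73.5% | 23.7% |
| True DID 6 points, rho about 0.29 | 46.5% | 59.5% | 58.8% | 12.2% |

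In every disagreement the mixed model was significant and the pooled regression was not. With girl-clustered standard errors the linear regression rejects almost as often as the mixed model.

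**The case against.** The strongest reply is that the plan already ranks the tests. The mixed model is called the primary comparison of the binary outcomes, it carries a girl-level random effect, and every Table 4 indicator falls under it. The regression equation gives only a mean structure and does not rule out clustered standard errors. A condensed article may leave that choice to the full plan, and the equation may be generic DID algebra or may be meant for continuous KAP scores.

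Much of this stands. The label favours the mixed model, and clustering would remove the problem. But the article does more than omit a detail. It says that the significance of the DID is tested with that equation, names its coefficient as the treatment effect and attaches the 0.05 threshold to it. It does not restrict the equation to continuous scores, and the listed outcomes are binary.

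A reader might infer three stronger points, which the documents do not support:

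- That two tests let the more favourable p-value be chosen, with more false positives. In the simulations the favourable result was always that of the model already labelled primary, and that model held its level (4.8%).
- That the Z-test or t-test on the KAP variables ignores pairing. The sentence notes that the answers come from the same respondent. It could mean a paired test, or arm against arm at each survey, which is valid. It needs clarifying; it is not a proven error.
- That the primary effect must be a standardised risk difference because Table 4 is in percentages. An odds ratio is a legitimate measure, so this is a reporting preference.

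**Conclusion.** The point holds in a limited form. The plan states two significance tests for one effect, and the one without a participant term, run as written, has the wrong standard error. The sizes shown depend on two assumptions: a positive rho, which the documents do not give, and independence-based standard errors, which the equation implies but does not spell out. At rho 0.3 to 0.5 the standard error is 20% to 41% too large, and 80% power becomes about 68% to 51%. At rho 0 nothing is lost.

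The direction is conservative. The two tests may differ on significance, but this does not mean effects of opposite sign. The analysis labelled primary is not itself at fault. The conflict is worth correcting before analysis because the sentence on testing the DID remains in force beside the mixed model.

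**What to change.** In the Data analysis plan:

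1. State that the mixed-effects logistic model is the only confirmatory test of the DID for the binary outcomes.
2. Keep the linear DID regression only as a supportive estimate in percentage points, with girl-clustered standard errors or girl fixed effects, and reword the sentence that assigns the significance of the DID to it.
3. State that any within-arm comparison of baseline with follow-up uses a paired test: McNemar for proportions, paired t for scores.

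The cost is a few sentences and a clustering option in Stata. No new data are needed, and the sample size and the primary model do not change.

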**Methods:**

A two-arm RCT will be conducted in three cities in India: Patna, Jaipur, and Delhi-NCR. The first arm is the treatment (encouragement) arm (n = 975) where the participants will be encouraged to download and play the game, and the second arm (n = 975) where the participants will not receive any nudges/encouragement to play the game. They may or may not have access to the game. After the baseline recruitment, participants will be randomly assigned to these two arms across the three locations. Participants of the treatment/encouragement arm will receive continuous support as part of the encouragement design to adopt, install the game from the Google Play Store at no cost, and play all levels on their Android devices. The encouragement activity will continue for ten weeks, during which participants will receive creative messages via weekly phone calls and WhatsApp messages. We will conduct the follow-up survey with all the participants (n = 1950) from the baseline survey after ten weeks of exposure. We will conduct 60 in-depth qualitative interviews (20 at each location) with a sub-sample of the participants from the encouragement arm to augment the quantitative surveys.

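### The primary difference-in-differences test keeps a free arm effect at baseline and does not adjust for each girl's baseline response: valid under randomisation, but it gives up (1−ρ)/2 of the effective sample

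*Protocol article*

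**What the plan says.** All of the analysis text is in the protocol article, Data analysis plan.

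- **Model.** The primary comparison of binary outcomes "will use mixed-effects longitudinal logistic regression, with random effects for the individual over time".
- **Role of baseline.** "The baseline will be included as a time point only".
- **Treatment effect.** The arms are compared by difference-in-differences: "Statistically, this amounts to testing for an interaction between time and treatment arm in the longitudinal model".
- **Arm main effect.** In the DID regression equation, "b_1_ and b_2_ are slopes for the study arm and time, respectively", with a third coefficient for the treatment effect.
- **Adjustment.** The primary analysis is described as unadjusted. Covariates such as age and education enter only in secondary models, alongside time and arm, by backward selection at 0.15. The plan itself says these models may improve precision.

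On size and allocation, the Sample size section states: "The study proposes recruiting 1,950 participants from three sites: 650 girls each from Patna, Jaipur, and Delhi NCR for in-person interviews", of whom "half of the participants (i.e., 325 girls each from Patna, Jaipur, and Delhi NCR) will receive nudges/encouragement to play the game". No correlation between baseline and follow-up, power, target effect or expected prevalence is shown.

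**The concern.** Individual randomisation makes the expected baseline level the same in both arms. A model with a free arm effect at baseline does not use that fact. It estimates a baseline difference known to be zero in expectation and subtracts the estimate, noise included, from the follow-up difference. Adjusting for the baseline response, or constraining the arms to be equal at baseline, uses the same data and avoids that noise.

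Precision matters in this trial. The primary analysis is by intention to treat, control girls may have access to the game anyway, and encouraged girls need not play it. The effect of encouragement is therefore likely to be diluted, and wider intervals make it easier to miss.

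The planned secondary models are not a substitute. In a linear DID with both time points present for every girl, a fixed covariate entered as a main effect cancels and leaves the interaction unchanged. The variable that would help, her own baseline response, is not used as a covariate in the primary model.

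**Working it through.** **Inputs from the article.** 1,950 girls, 975 per arm (3 × 650 = 2 × 975 = 1,950; 3 × 325 = 975, so the counts agree). Significance level: "A probability value of less than 0.05 will be considered statistically significant for all statistical tests conducted". How 1,950 was arrived at cannot be reproduced, because the inputs to the sample size estimation are not shown.

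**Assumptions.** ρ from 0.1 to 0.9; two-sided test; 80% power; 50% prevalence for the detectable differences; 975 complete pairs per arm.

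**Step 1, linear variances**, in units of 2σ²/n with n per arm:

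- DID: 2(1−ρ)
- follow-up only: 1
- adjusted for baseline: 1−ρ²

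The ratio of DID to adjusted variance is 2(1−ρ)/(1−ρ²) = 2/(1+ρ). DID therefore keeps (1+ρ)/2 of the effective sample and loses (1−ρ)/2. DID is worse than follow-up only when 2(1−ρ) > 1, that is, when ρ < 0.5.

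**Step 2, numbers.** The detectable difference is (1.960 + 0.842) × √(2 × 0.25/975) × √(variance in the units above) = 6.34 points × √(variance). The last column is the power of DID if the adjusted analysis had 80%.

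| ρ | Variance ratio | Loss | 1,950 girls are worth about | Detectable difference, DID v adjusted (points) | DID power |
|---|---|---|---|---|---|
| 0.1 | 1.82 | 45% | 1,072 | 8.5 v 6.3 | 55% |
| 0.3 | 1.54 | 35% | 1,268 | 7.5 v 6.1 | 62% |
| 0.5 | 1.33 | 25% | 1,463 | 6.3 v 5.5 | 68% |
| 0.7 | 1.18 | 15% | 1,658 | 4.9 v 4.5 | 73% |
| 0.9 | 1.05 | 5% | 1,853 | 2.8 v 2.8 | 78% |

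**Step 3, check in the planned type of model.** Expected-data likelihood for a random-intercept logistic model, 975 per arm, with assumed rates. The loss is 1 minus the squared ratio of the Wald z for the interaction to the Wald z for arm in a logistic regression of follow-up on arm and baseline. Correlation here is that of the binary responses in the control arm.

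| Control rate, baseline to follow-up | Correlation | Loss | Linear formula |
|---|---|---|---|
| 50% to 55% | 0.31 | 34% | 34% |
| 50% to 55% | 0.51 | 24% | 24% |
| 30% to 35% | 0.30 | 38% | 35% |
| 30% to 35% | 0.50 | 28% | 25% |
| 15% to 20% | 0.33 | 41% | 34% |
| 15% to 20% | 0.46 | 35% | 27% |

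The formula is close at mid-range prevalence and understates the loss for rarer outcomes. Dropping only the arm main effect recovers nearly all of it. With control rates of 30% to 35% and correlation 0.38, z is 2.78 for DID, 3.41 for the constrained model and 3.42 for baseline adjustment.

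**Step 4, site.** A site effect that is constant over time cancels in a linear DID. Adding site to the baseline-adjusted comparator moves the relative efficiency of DID as follows:

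| Assumed site prevalences | ρ = 0.33 (0.665 without site) | ρ = 0.50 (0.750 without site) |
|---|---|---|
| 30/35/40% | 0.663 | 0.748 |
| 20/35/50% | 0.641 | 0.732 |
| 10/35/60% | 0.590 | 0.694 |

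None of the loss in Step 2 comes from site, and a site term adds materially only if the sites differ very widely.

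**The case against.** **The sentence on baseline does not by itself show the defect.** This stands. A constrained-baseline model also treats baseline as a time point. The inefficiency comes from the free arm effect, and the evidence for that is the arm slope in the DID equation and the description of the adjusted models as adding covariates to time and arm.

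**The size is not in the documents.** This stands. A reader might infer that a quarter to a third of the sample is lost. That holds only for ρ between about 0.33 and 0.50, and the article gives no ρ. If outcomes are stable within girls, the loss is small. Imputing missing follow-up from the worse half of each arm's distribution would also alter the correlation in the analysed data.

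**Site.** A reader might infer that omitting site is part of the loss. It is not (Step 4). Stratified allocation is not stated either: the abstract says that "participants will be randomly assigned to these two arms across the three locations", and only the count of 325 encouraged girls per site implies balance. A site term can reasonably be left to an analysis plan, and the covariate examples for the secondary models do not exclude it.

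**Validity and power.** A reader might infer that the result is biased or the trial underpowered. Neither follows. Under randomisation the DID contrast is valid, as the plan says, and the sample size may have been set for a DID analysis.

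**DID may be the safer choice if baseline follows allocation.** This is the most substantial objection. The abstract randomises after baseline recruitment. Table 2 puts the baseline assessments in the post-allocation column, alongside the intervention arrow, and the Randomization section works from the list made after household screening, with unblinded researchers. If allocation came first, differential consent or early exposure could make the arms differ at baseline. Constraining them to be equal could then introduce bias, while DID would remove a difference that is constant over time. This makes the remedy conditional. It does not fully rescue DID, because a baseline taken after encouragement had begun would compromise that too.

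**Conclusion.** The point holds as one of efficiency. With baseline measured before allocation, the planned primary test is less precise than a baseline-adjusted one at every ρ below 1, and less precise than ignoring baseline when ρ is below 0.5. The direction needs no assumed figure. The size does: (1−ρ)/2, from 45% at ρ = 0.1 to 5% at ρ = 0.9, and somewhat more for low-prevalence outcomes in the logistic model. The calculations assume complete pairs. The planned covariate models do not recover the loss. The plan should be changed, but the trial's validity is not in question on this ground.

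**What to change.** 1. Reconcile the abstract with Table 2 and state whether baseline is completed before allocation. The remaining steps depend on that being so.
2. Make the primary model one of the following:
   - the planned mixed-effects logistic model without the arm main effect (time, arm × follow-up, random girl effect); or
   - a logistic regression of the follow-up outcome on arm and the girl's own baseline response.
3. Report a standardised risk difference with its 95% confidence interval.
4. Keep the DID table as description.
5. A site term may be added, because 325 encouraged girls per site implies balance by site. This is good practice and is not what recovers the loss.

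The cost is a short change to the model specification and a clarified schedule table. No extra data, participants or software are needed.
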